#### Inclusion and Exclusion Criteria

Target participants will be mainly community-dwelling elderly people who are living in Shanghai. The specific inclusion and exclusion criteria are listed in Table 2. The participants will quit the study if they have been diagnosed with severe diseases (such as heart failure) or serious adverse events occur during the experiment. Besides, the participants will be allowed to voluntarily quit as result of any of their own reasons. We plan to execute the following ways to access our participants as many as possible: (1) Distributing study recruitment flyers in nearby four communities with permission; (2) Sending study recruitment presentations to community healthcare center staff to help introduce potential participants; and (3) Disseminating the recruitment information through electronic communications and anyone interested can contact the recruiter by telephone.

**TABLE 2 T2:** Inclusion criteria and exclusion criteria.

Inclusion criteria	Exclusion criteria
Aged 50–80 years, can speak Chinese and complete the questionnaire survey.	Have practiced tai chi regularly for any reason within the past 6 months or who have practiced tai chi, yoga or qigong for nearly half a year to treat LBP.
Pain, at least 3 months, typically occurs in the area between the lower rib margins and the buttock creases, commonly accompanied by pain in one or both legs.	Have received guided physical therapy for LBP within half a year, including stretching, strength training, motor control training, and so on.
Have had back pain on at least half the time in the last 6 months.	Have specific causes or potential causes of LBP (e.g., sciatica, spinal stenosis, lumbar disk herniation, spondylolisthesis, recent vertebral fracture, and so on).
The average scores of numerical rating scale (in the range of 0–10) ≥3 and ≤8.	Have red flags of serious underlying systemic or visceral disease (e.g., inflammatory disorders malignancy, unexplained weight loss, infections, or recent trauma).
Back-related function scores of Roland-Morris disability questionnaire (in the range of 0–24) ≥5.	Pain in other parts of the body is greater than low back pain.
Have normal cognition or only mild cognitive impairment [the scores of Mini-Mental State Examination (in the range of 0–27) ≥24].	Had prior lumbar spine surgery.
Able to understand the learning process and complete the whole course.	Have history of drug and alcohol abuse.
Volunteer to participate the trial and sign an informed consent.	Have other disabling conditions that might confound treatment effects.
	Have moderate to severe depressive symptoms [the scores of Geriatric Depression Scale (in the range of 0–30) ≥21].
	Exercise is contraindicated.

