**Methods:**

We will perform a single-blind randomized controlled trial on elderly people with chronic low back pain. 138 participants will be randomly assigned to the Tai Chi Quan group (60-min classes, three times per week for 12 weeks) or physical therapy group (10 min of evaluation and warm-up, 40 min of therapist-directed exercise therapy, and 10 min of relaxation, three times per week for 12 weeks) with an allocation of 1:1. The participants will be followed up for 40 weeks for the study of long-term effects. The primary outcomes include pain intensity and back-related function at 12 weeks. Secondary outcomes include lumbar quantitative sensory testing, balance, cognitive function, psychosocial function, cost-effectiveness, compliance and adverse events. We will perform the intention-to-treat analysis for withdrawal and missing data.

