**Secondary outcomes**				
Lumbar quantitative sensory testing	√	√		
4-stage balance test				
Trial making tests	√	√	√	√
Stroop test	√	√	√	√
6-min walk test	√	√	√	√
Geriatric depression scale	√	√	√	√
Self-rating anxiety scale	√	√	√	√
Pain catastrophizing scale	√	√	√	√
Tampa scale for Kinesiophobia	√	√	√	√
Pittsburgh sleep quality index	√	√	√	√
Short-form 12	√	√	√	√
General perceived self-efficacy scale	√	√	√	√
Expenses for healthcare monthly	√	√	√	√
Expense for other diseases	√	√	√	√
Expense for low back pain	√	√	√	√
Global perceived effect		√		
Adherence		√		
Adverse Events		√		

*NRS, numerical rating scale; RMDQ, Roland Morris disability questionnaire.*

The study setting is located in the Center of Sports Medicine and Rehabilitation, Shanghai Shangti Orthopaedic Hospital (SSOH), Shanghai, China. Each participant will sign a written informed consent. This study protocol has been approved by the Ethics Committee of the Shanghai University of Sport, China (Grant number 102772019RT039).

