##### Exercise Intensity Monitoring

Given that our participants are mainly elderly people, exercise intensity will be closely monitored throughout the study. During the learning phase, participants will be instructed to exercise at which their rating of perceived exertion (RPE) is characterized as being “light to moderate” (Scherr et al., 2013). In the last 8 weeks, the intensity progresses to “moderate” (equals to 4–6 scores). Exercise intensity will be assessed weekly by the class assistant. All participants need to record their weekly home exercise and adverse events on the given file after class (see Supplementary Additional File 1).

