##### Exercise Intensity Monitoring

For a more clinical setting, the 40 min of exercise intensity is controlled by the therapist’s evaluation of the participant. According to RPE, moderate intensity aerobic exercise equals to 4–6 scores of the modified Borg Scale. Participants shall record their weekly home exercise and adverse events on given file (see Supplementary Additional File 4).

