#### Global Perceived Effect

Global Perceived Effect (GPE) numerical rating scale consists of seven choices (from 1 to 7 points), each representing the overall improvement in the participants’ symptoms after they completed the trial (Kamper et al., 2010). A good improvement indicates a high score. It can be useful in understanding the strengths and shortcomings of outcome measures for research. The participants will be asked to rate the degree of improvement or aggravation in their conditions since the beginning of the intervention. The GPE has an excellent test-retest reliability with an ICC of 0.90 (Kamper et al., 2010).

We will record the number of classes the participants attend and the reasons for absence. In addition, adverse events, which are related to interventions and home exercise, will be recorded (see Supplementary Additional Files 1, 4 for details).

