### Data Analysis

Intention-to-treat analysis will be performed regardless of adherence. Microsoft excel 2016 and IBM SPSS Statistics 20.0 (SPSS Inc., Chicago, IL, United States) will be used in data analysis. Continuous variables (e.g., age, body mass index, NRS score, and RMDQ score) will be represented as mean ± standard deviation and be compared using analysis of the independent samples *t*-test. We will use the chi-squared test to analyze the categorical variables (e.g., gender, marital status, smoking, and exercise habits) between the TCQ group and PT group. The baseline demographics characteristics differences between groups will be compared using analysis of *t*-test, variance (ANOVA) or chi-squared tests. If potential confounding factors including gender, age, body mass index, smoking, exercise habits, etc., are present, we will prespecified an adjusted analysis, by using multiple linear regression. At the same time, missing values at week 12, 26, and 52 will be imputed using the multiple imputation.

The co-primary outcomes are the measurement of minimal clinically important difference in NRS and RMDQ scores in two groups after the 12-week intervention, and the paired-sample *t*-test will be carried out for the comparison of the differences. For secondary outcomes, the difference of continuous variables between groups will be compared using the analysis of independent-samples *t*-test. Expenses for LBP or other disease will be explored for cost-benefit analysis. Participants’ global perceived effect, adherence, and health-related quality of life will be compare using appropriate regression. The Fisher exact test will be used to compare adverse events. For the follow-ups phase, two-way repeated-measures analysis of variance (group × time) will be carried out to assess the differences of the primary outcomes (NRS score and RMDQ score) between the two groups. In all analyses, a *P*-value of <0.05 will be considered statistically significant.

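### The exit rule takes participants with new severe disease or a serious adverse event out of the study, not only the classes, and the protocol is inconsistent on which adverse events are recorded

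*Protocol article*

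**What the plan says.** **Leaving the study.** Inclusion and Exclusion Criteria: "The participants will quit the study if they have been diagnosed with severe diseases (such as heart failure) or serious adverse events occur" during the trial. The next sentence treats voluntary quitting as a separate matter. No section says whether anyone who leaves under the first rule is assessed again.

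**Analysis.** Data Analysis: "Intention-to-treat analysis will be performed regardless of adherence", and "missing values at week 12, 26, and 52 will be imputed using the multiple imputation". The abstract adds: "We will perform the intention-to-treat analysis for withdrawal and missing data".

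**Adverse events.** Three places describe what is recorded:
- The paragraph closing the Global Perceived Effect section, citing Additional Files 1 and 4: "adverse events, which are related to interventions and home exercise, will be recorded".
- Exercise Intensity Monitoring, Tai Chi Quan group (Additional File 1): "All participants need to record their weekly home exercise and adverse events on the given file after class".
- Exercise Intensity Monitoring, physical therapy group (Additional File 4): "Participants shall record their weekly home exercise and adverse events on given file".

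Table 1 gives the row "Adverse Events" a single tick, which by its position falls under week 12. Data Analysis compares adverse events between arms with Fisher's exact test. Randomization and Blinding accepts that participants cannot be blinded.

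**The concern.** Stopping an intervention and leaving a study are different events. An intention-to-treat comparison needs outcomes from people who stop as well as from those who continue. The exit rule merges the two for people whose health has deteriorated, so it creates missing outcomes by design, and for a reason tied to health. Standard multiple imputation assumes that data are missing at random given what was observed. If everyone with such an event leaves, nobody remains in the data to show what happens after one.

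The cost outcome is exposed in the same way. Expenses for Healthcare Monthly covers spending on back pain and on other diseases, and states an expectation that Tai Chi Quan will lower the cost of treating chronic disease. Someone newly diagnosed with, say, heart failure is likely to be among the higher spenders, and that person's later expenses are the ones that drop out.

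On safety, if only related events are recorded, a causal filter has been applied before the arms are compared. With unblinded participants, that filter may work differently for a Tai Chi class and for therapist-led exercise.

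**Working it through.** **1. The plan's own figure.** Inputs from Sample Size: effect size 0.54, two-sided alpha 0.05, power 0.80, 20% attrition. The two-sample t-test needs 54.81, rounded up to 55 per group. Then 55 / 0.80 = 68.75, rounded up to 69 per group and 138 in total, as stated. Power is 0.801 with 55 per group and 0.883 with 69. The plan therefore already allows for a loss of numbers; the issue here is who is lost.

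**2. Shift in the RMDQ difference.** The documents give no rate of exits and no outcome for those who leave, so both are assumed. Let q1 and q2 be the proportions leaving each arm under the rule, and d the amount, in SD, by which leavers' true scores are worse than the values imputed for them.

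Shift in one arm's mean = q × d. Shift in the difference between arms = (q1 − q2) × d, in favour of the arm with more exits.

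| q1 | q2 | d = 0.5 SD | d = 1.0 SD |
|---|---|---|---|
| 2% | 2% | 0 | 0 |
| 5% | 5% | 0 | 0 |
| 5% | 2% | 0.015 | 0.030 |
| 10% | 5% | 0.025 | 0.050 |

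**3. In RMDQ points.** If the 3-point minimal important difference and the effect size of 0.54 belong together (an assumption; Sample Size does not say so), then SD = 3 / 0.54 ≈ 5.6 points. The non-zero entries run from 0.015 × 5.6 ≈ 0.08 points to 0.05 × 5.6 ≈ 0.28 points. Against the design effect, 0.05 / 0.54 ≈ 9% at the top of the range and 0.015 / 0.54 ≈ 3% at the bottom.

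**4. A harsher case.** If 5% leave one arm and none leave the other, a gap of 0.5 to 1 SD gives 0.025 to 0.05 SD, about 0.14 to 0.28 points. A gap of 6 to 8 points would give 0.05 × 6 = 0.3 to 0.05 × 8 = 0.4 points at 5%, and 0.6 to 0.8 points at 10%. But 6 / 5.6 ≈ 1.1 SD and 8 / 5.6 ≈ 1.4 SD, which is a large gap on a back-specific scale, and these figures reach the arm difference in full only if every exit falls in one arm.

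**5. Adverse events, side by side.** The Global Perceived Effect paragraph limits recording to events related to the interventions and home exercise, and points to Additional Files 1 and 4. The two Exercise Intensity Monitoring sections describe those same files as weekly participant records of adverse events, without that limit. Both cannot define the data set for Fisher's test. Under the limited reading, unrelated events never enter it; under the other, they do. No arithmetic applies.

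**The case against.** The strongest reply is that a journal article condenses the full protocol. Follow-up after discontinuation may be set out there, and leaving the study may have been loose wording for leaving the programme. Intention-to-treat regardless of adherence concerns analysis as assigned. The abstract anticipates withdrawals, and multiple imputation keeps every randomised participant in the analysis. Much of this stands. There is no formal contradiction with intention-to-treat, and it is an inference that no later data will be collected. What remains is that the article does state a rule, sets it apart from voluntary quitting, and names the study as the thing left. Imputation keeps the person in the analysis but does not supply the outcome that followed the event.

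A reader might infer more on safety: that only related events are recorded, that participants or class staff decide relatedness before anything is written down, and that falls or cardiac events called unrelated disappear. The documents do not support this. The two monitoring sections have participants record adverse events without any causal limit. No passage says who judges relatedness or when; the class assistant's stated task there is exercise intensity. The exit rule carries no relatedness condition, so serious events have to be identified for it to be applied at all.

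A reader might also infer a material bias in efficacy. That needs large gaps and one-sided exits, neither of which has a source in the documents.

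**Conclusion.** The point holds in a limited form. As written, the exit rule produces health-related gaps in NRS, RMDQ and expense data that multiple imputation cannot be relied on to fill. This weakens the intention-to-treat analysis and the cost comparison.

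The effect on the RMDQ difference is probably small: 0.015 to 0.05 SD under the assumed imbalances, and zero when exits and gaps are equal across arms. It grows only if exits differ markedly by arm. The effect on costs cannot be sized from the documents.

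For adverse events, the finding is an inconsistency between sections. Only under the narrower section's reading does Fisher's test rest on events filtered by relatedness in a trial with unblinded participants. The change is worth making because neither uncollected outcomes nor unrecorded events can be recovered at analysis.

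**What to change.** - **Exit rule.** Leave the rule for stopping exercise as it is. Add that a participant who stops under it remains in the study for follow-up and continues to give NRS, RMDQ and expense data at the planned week 12, 26 and 52 visits, unless consent to follow-up is withdrawn.
- **Adverse-event recording.** Reconcile the Global Perceived Effect paragraph with the two Exercise Intensity Monitoring sections, so that all adverse events in both arms are recorded on the existing weekly files, with relatedness held as an attribute of each event and not as a condition for recording it.
- **Adverse-event analysis.** Apply Fisher's exact test to all events and to serious events first, and to related events second.

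The cost is rewording of the exit rule and the adverse-event text, plus a few extra contacts within visits already planned. No additional blinded assessor is needed.

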### Intervention Conditions

#### Intervention Classes Locations

The participants randomized to TCQG will practice it at community health centers or residential activity center for non-profit organizations where the evidenced-based prevention of chronic diseases and health promotion activities are encouraged. PT intervention will take place at the Center of Sports Medicine and Rehabilitation of SSOH or community resident activity centers.

#### Tai Chi Quan Group

Tai Chi Quan is strongly recommended for treating CLBP (Qaseem et al., 2017). In our study, the TCQ program features eight modified movements, which combine Yang style and Cheng style, and reflect multiple directions around the central axis. In general, these movements revolve around the waist as the core, thereby activating the limbs. The movements include various steps (forward, backward and lateral), spatial orientation movements (performing each single movement in different directions) and complex movements (requiring coordination of eyes-heads-hand and increasing demands on attention and postural control) (Li, 2014). TCQ is a body–mind exercise, coordinating the movement of the limbs through lumbar winding movements (McAnulty et al., 2016). Therefore, TCQ may provide more stimulation for core muscles and improve the flexibility and stability of the spine. It may also enhance directly transferable skills in daily life, such as reaching and turning, going up/down stairs and walking.

##### Protocol

The eight movements have been demonstrated in our published article (R. Wang et al., 2022). The eight movements combine forward and backward steps, left and right steps and diagonal steps with rotating waist. The consistent exercise schedule includes three parameters: frequency (three times a week), time (60 min per session) and content (10 min of warm-up, eight core forms and 5 min cool-down). Method of inhaling and exhaling will be integrated into the TCQ forms. During the initial 3 weeks, classes will focus on learning these eight forms. At the fourth week, participants will learn to unite the forms. In the last 8 weeks, classes will concentrate on practice. To ensure the best curative effect, we conduct TCQ classes for participants with qualified coaches who finished training delivered by senior TCQ professor before the intervention classes. Apart from a coach, each class is provided with an assistant to provide right action feedback to the participants.

##### Exercise Intensity Monitoring

Given that our participants are mainly elderly people, exercise intensity will be closely monitored throughout the study. During the learning phase, participants will be instructed to exercise at which their rating of perceived exertion (RPE) is characterized as being “light to moderate” (Scherr et al., 2013). In the last 8 weeks, the intensity progresses to “moderate” (equals to 4–6 scores). Exercise intensity will be assessed weekly by the class assistant. All participants need to record their weekly home exercise and adverse events on the given file after class (see Supplementary Additional File 1).

#### Physical Therapy Group

After physical examination and special lumbar tests, we will divide the group into four types (type 1: LBP with mobility deficits; type 2: LBP with movement control impairment; type 3: LBP with referred pain; type 4: LBP with radicular pain) according to the World Health Organization’s International Classification of Functioning, Disability, and Health (Delitto et al., 2012) and the American Physical Therapy Association (APTA) clinical guideline of LBP (George et al., 2021). Different types of participants receive different types of exercises, such as position adjustment, flexibility exercise, stability exercise, specific trunk muscle activation exercise, McKenzie directional repetitive technique, and neural mobilization (see Supplementary Additional File 2). These exercise recommendations are based on the latest APTA guideline of LBP (George et al., 2021). The same therapist is responsible for in-group exercise for the same type of participants. The whole process will be implemented by the licensed therapist who have finished the prescribed training on the classification assessment and intervention, and recorded in the Classified Assessment and Intervention Form (see Supplementary Additional File 3).

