### Sample Size

The sample size analysis is based on hypothesized change in RMDQ scores. For the primary outcome of change in pain intensity from baseline to week 12, we assume that two-sided α error prob is equal to 0.05 and power is 0.8. The minimal clinically important difference of the RMDQ is prespecified for 3 points (Jordan et al., 2006), and the effect size of RMDQ is in the range of 0.54–0.84 (Saper et al., 2017). We used G-Power Software (version 3.1.9.2, Germany) to estimate the total sample size with the method of *t*-tests-means (difference between two independent means measures in two groups). Considering the effect size of RMDQ is 0.54 and 20% attrition rate, we need a minimum of 138 participants in this study or 69 participants in each group to detect whether 12 weeks of TCQ and grouped-PT have a significant clinical effect on CLBP.

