### Participants

#### Randomization and Blinding

We will take a community randomized approach, and four communities will be assigned with an allocation of 1:1 through the random numbers generated by the analyst. Finally, two communities will be assigned to the TCQG, and two to the PTG. We will recruit participants in the corresponding community to practice TCQ or PT. Throughout the courses of the trial, all study assessors who are responsible for collecting outcomes will be blinded to the hypotheses and allocation. Meanwhile, we shall maintain separation between the assessors and assistants who are responsible for recruitment work and between the assessors and class instructors. In addition, participants should conceal their group status to the assessors. Participants have informed consent and are blinded impossibly without a placebo. Finally, all data analyst do not know group allocation and deal with coded data instead of the names of the participants.

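### Both treatments are given in coach- or therapist-led groups, but the sample size and every named between-arm test assume independent participants, so the stated 80% power and 0.05 level do not hold if outcomes correlate within a class

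*Protocol article*

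**What the plan says.** **Delivery.** Under Tai Chi Quan Group, Protocol, participants are taught in classes: "Apart from a coach, each class is provided with an assistant to provide right action feedback to the participants". Under Physical Therapy Group, participants are sorted into four low back pain types and exercise in type-based groups: "The same therapist is responsible for in-group exercise for the same type of participants". Both programmes run three times a week for 12 weeks.

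**Sample size.** The calculation is a t-test for a "difference between two independent means measures in two groups", with "two-sided α error prob is equal to 0.05 and power is 0.8". The inputs are given as "Considering the effect size of RMDQ is 0.54 and 20% attrition rate", and the result is "we need a minimum of 138 participants in this study or 69 participants in each group". Attrition is the only inflation.

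**Analysis.** Data Analysis states: "For secondary outcomes, the difference of continuous variables between groups will be compared using the analysis of independent-samples" t-tests. It also names chi-squared tests, Fisher's exact test, multiple linear regression for adjustment, and a group-by-time repeated-measures ANOVA for the primary outcomes over follow-up. None has a class, coach or therapist term.

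**Allocation.** Randomization and Blinding states: "We will take a community randomized approach, and four communities will be assigned with an allocation of 1:1". The Abstract and Study Design read as individual assignment.

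**The concern.** People who attend the same class share an instructor, a pace and one another's company over 36 sessions (3 × 12). Their outcomes may therefore be more alike than those of people in different classes. A test that ignores this gives a standard error for the Tai Chi Quan versus physical therapy difference that is too small, and one strong or weak instructor can pass for a treatment effect.

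The second hypothesis in the Introduction is that Tai Chi Quan is not inferior to physical therapy. Confidence intervals that are too narrow make that claim easier to reach.

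This does not depend on the unit of randomisation: the classes exist even if each person is allocated individually. A repeated-measures ANOVA does not deal with it either, because it models correlation within a person, not within a class. Nor can it be left to an analysis plan, since the article itself fixes the sample-size model and names the tests.

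**Working it through.** **1. The plan's figure.** Inputs from Sample Size: effect size 0.54, two-sided α 0.05, power 0.80, attrition 20%. The noncentral t calculation gives 55 per arm (power 0.801), or 110 in total. 110 / 0.8 = 137.5, rounded up to 138, or 69 per arm. The stated figure reproduces exactly, so it contains no design effect.

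**2. Inputs that the protocol does not give.** ICC and class size are assumptions. ICC is taken from 0.01 to 0.10. Class size m is 8 or 14 analysed participants; 14 corresponds to about 55 analysed people spread over four physical therapy types (55 / 4 ≈ 14).

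**3. Formulas.**
- Design effect: DE = 1 + (m − 1) × ICC
- Effective size per arm: 55 / DE
- Power at a true 5% level: Φ(0.54 × √(55 / DE / 2) − 1.96)
- False-positive rate of the plain test: 2 × [1 − Φ(1.96 / √DE)]

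Example with m = 14 and ICC 0.05: DE = 1 + 13 × 0.05 = 1.65. The effective size is 55 / 1.65 = 33.3 per arm. Power = Φ(0.54 × √16.67 − 1.96) = Φ(0.24) ≈ 0.60. The false-positive rate = 2 × [1 − Φ(1.526)] ≈ 0.127.

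**4. Results.**

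| Class size | ICC | DE | False positives, plain t-test | Power at 0.54 | Total N for 80% power |
|---|---|---|---|---|---|
| any | 0 | 1.00 | 5.0% | 81% | 138 |
| 8 | 0.01 | 1.07 | 5.8% | 78% | 148 |
| 8 | 0.05 | 1.35 | 9.2% | 68% | 188 |
| 14 | 0.05 | 1.65 | 12.7% | 60% | 228 |
| 14 | 0.10 | 2.30 | 19.6% | 46% | 318 |

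The 81% in the first row is the normal approximation; the t-test value is 80.1%. Total N is 55 × DE rounded up, divided by 0.8 and rounded up, then doubled.

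**5. Check by simulation.** With four classes of 14 per arm and 20,000 trials per setting, the plain t-test rejects a true null in 12.8% of trials at ICC 0.05 and 19.6% at ICC 0.10. A class-level t-test (6 degrees of freedom) holds 5%, but its power at 0.54 is 46% and 36%. Part of that loss comes from the few degrees of freedom: at ICC 0 the same test has 66% power. The normal-approximation powers in the table are therefore optimistic when classes are few.

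**The case against.** **The size is assumed.** The protocol gives no ICC, class size or number of coaches. At ICC 0 nothing is lost, and at ICC 0.01 with classes of 8 the loss is small. A reader might infer that the 80% power and 5% level certainly fail. The documents do not support that; they support a conditional statement with a range. This part stands.

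**Not every comparison is covered.** Global perceived effect, adherence and quality of life are left to a regression whose form is not given. The week-12 co-primary comparison is worded as a paired-sample t-test, which is not a between-arm test, although the sample size is for one. The point therefore reaches every between-arm test that the plan names, not every comparison it will make.

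**In the physical therapy arm, therapist and pain type coincide.** Groups are formed by type, so likeness within a group may come from the patients rather than from treatment. A simulation assumed 56 per arm, types explaining 5% or 10% of outcome variance in both arms, and no therapist effect. The plain t-test held its level (4.9% and 5.3%). A class-level test that treated types as clusters was conservative (2.3% and 1.2%), and its power fell to 51% and 37%, against 81% for the plain test. This stands as a limit on the remedy. It does not make independence a safe assumption. The text also does not exclude one therapist covering several types, in which case therapist could not be separated from arm.

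**Class variance is hard to estimate.** With four classes of 14 at ICC 0.05, a simple estimate of one arm's class variance was zero or negative in 37% of simulations. This argues against insisting on arm-specific variances.

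**The community problem is larger.** With two communities of 28 analysed per arm and ICC 0.05, the plain test has 20.0% false positives and a community-level test has 20% power. If Tai Chi Quan classes sit within communities, community-level analysis would absorb their effects. It need not do so for physical therapy: sessions may be held at the hospital centre, so a therapist's group could draw on both communities. That is possible, not stated. In simulations with such crossing, no community effect and therapist ICC 0.05, a community-level test had about 6.4% to 6.6% false positives. What remains is modest but not zero.

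**Conclusion.** The concern holds in conditional form. The plan delivers both arms in led groups, yet it sizes the trial and names its between-arm tests as if participants were independent. Whenever the within-class correlation is above zero, the confidence intervals are too narrow and the power is below the stated 80%.

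Under the assumed layouts the effect runs from slight (classes of 8, ICC 0.01) to serious (four classes of 14 per arm, ICC 0.10). The protocol does not say where in that range the trial lies.

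The point is separate from the randomisation of two communities per arm and ranks below it. It would remain if allocation were settled as individual. It should be corrected, but it does not by itself invalidate the trial.

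**What to change.** 1. **Record** each participant's class and coach or therapist. Classify pain type at baseline in both arms if the existing assessment allows it.
2. **Analyse** between-arm differences in NRS, RMDQ and the continuous secondary outcomes with a linear mixed model. Include a class/therapist random effect and small-sample degrees of freedom, and use a common variance if arm-specific variances cannot be estimated. This is in addition to whatever is done for community.
3. **State the limit:** in the physical therapy arm, therapist and pain type are confounded. The random effect cannot separate them and may be conservative unless type is adjusted for.
4. **Restate the power** in Sample Size. Present 80% as the power under independence only, and give power over a stated range of ICC and number of classes.

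**Cost:** one or two extra identifiers per participant, wider confidence intervals and a less favourable stated power. These changes need no extra patients, but restating the power does not restore it. Restoring 80% would take a total of 148 to 318 across the settings in the table.
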